### 2.3 Study design and data source

Routinely collected claims data from a large German statutory health insurance (BARMER) will be used to carry out the study. BARMER is the second largest statutory health insurance in Germany with about 8.6 million insured individuals (status of 2024). BARMER claims data are available on application for research purposes in anonymized data sets, hosted in a scientific data warehouse [in German: Wissenschaftliches Data Warehouse (WDWH)] by BARMER. Within the project VAC-MAC (in german: VACcinierung von MS/Arthritis/Colitis-Patient:innen, DRKS-ID: DRKS00031559, registered 28.08.2023), we have access to data from 2013 to 2021. VAC-MAC is a project funded by the German Innovations Fund (Innovationsfonds, grant number 01VSF21044) with multiple goals related to assessing and improving the vaccination coverage of individuals with MS, IBD, or CIRD.

The target population of all target trials consists of all individuals insured by the BARMER who fulfill the following inclusion criteria. The subject:

Has been enrolled in the BARMER health insurance company for at least 2 years before inclusion into the study with interruptions of no more than 5% of the total time.Is at least 18 years old at the start of observation.Has a biological sex of either male or female.Did not receive an organ transplantation in the last 2 years before inclusion into the study.Did not have any form of cancer in the last 2 years before inclusion into the study.Did not have an autoimmune-related disease other than MS, IBD, or CIRD in the last 2 years before inclusion into the study.

The start of the observation period/study is defined as the date on which an individual is included in the study during the trial emulation, as outlined in Section 2.6. In addition to these criteria, we also define one trial-specific inclusion criteria for each vaccine-effectiveness analysis. For the herpes zoster vaccine-effectiveness study, we require that the individual has not previously received a herpes zoster vaccination. Similarly, for the influenza vaccine-effectiveness trials, we require that the individual has not already received an influenza vaccination in the current influenza season.

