### 2.5 Measures

#### 2.5.1 Disease definitions

We will consider three main types of autoimmune disease groups: MS, CIRD, and IBD. To determine whether an individual has developed one or multiple of the diseases contained in each group at certain points in time using the BARMER data, we developed new algorithms based on previous research. For MS all existing subtypes of the disease are considered. Our algorithm to identify MS is loosely based on the algorithm developed by Culpepper et al. (34). We further define an individual to have CIRD only when that individual either has *rheumatoid arthritis, axial spondyloarthritis* or *systemic lupus erythematosus*. Those three diseases are each identified using different algorithms, based on previous work (35–37). Similarly, we define IBD to be present if the individual has *Crohn's disease* or *colitis ulcerosa*, which are also identified separately using algorithms based on previous research (38, 39). The exact definitions used for each disease and sub-disease are given in the online supplement of this article.

Through the course of the VAC-MAC project, these definitions have already been applied to the BARMER data. We were able to identify approximately 50,000 patients with MS, 300,000 patients with CIRD and 80,000 patients with IBD between the 01.01.2013 and the 31.12.2021. Additionally, approximately 9,000 of these patients had more than one of the three considered disease categories. Although this constitutes a “look into the data” before this study protocol was published, this procedure is in accordance with recommendations by Wang and Schneeweiss (40), who state that performing data checks before study registration actually increase the validity of the study.

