**Place (Place of residence)**	
The place of residence of the individual.	The first three digits of the postal code of an individual or the associated federal state will be used as a rough proxy for the place of residence.

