#### 2.6.1 Matching method

Due to the different target trials per vaccine of interest, the planned matching and analysis strategy also differs slightly. To analyze the effectiveness of the herpes zoster vaccine, a single matching process will be used. For the influenza vaccine effectiveness trials we will use the same procedure, with the only difference being that it will be performed separately for each influenza season. The matching will be carried out as follows.

For the previously defined start date of the respective trial, the eligibility of all individuals contained in the BARMER database will be determined using the above mentioned inclusion criteria. Eligibility will be checked using only the information available at that time. Every individual who was vaccinated with the vaccine of interest on this date is subsequently included in the dataset, in the treatment group. For every individual included in this way, we then include *k* further individuals who fulfill the inclusion criteria, but have not been vaccinated yet, in the control group. These controls will be matched exactly by age in years, gender, place of residence and disease group. If more than *k* potential controls are identified for a case, *k* controls will be picked at random from these. We will try to include 2 controls per case first (*k* = 2), but will lower this number to 1 if the number of available matches is insufficient. The date of inclusion equals “time zero” (27) for all individuals. Information about all relevant confounders is recorded as available on this date, corresponding to baseline information. This procedure is repeated on all subsequent days, until the emulated trial is over.

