Controls will be matched without replacement, meaning that individual *i* who was used as a control at one point in time *t* cannot serve as control more than once at the same point in time and can also not be used as control again at later points in time. However, people who have been used as controls will still be included in the trial later, if they get vaccinated. They will then be included in the treatment group, again with the vaccination date corresponding to the trial inclusion date. Information about the different defined outcomes are extracted from the BARMER data for each individual. This matching procedure results in datasets that are similar to what we would obtain if we actually had performed the respective target trials. The main advantage of this method is that it directly matches patients by inclusion-date, giving us a clearly defined “time zero” (27). Because controls are choosen to be similar to vaccinated individuals, this matching methods targets the *average treatment effect on the treated* (ATT) (56).

If no suitable control can be identified for a vaccinated individual at the time of vaccination, the individual is not included in the analysis. Because of the large amount of data, the long follow-up time and the fact that only a relatively small proportion of individuals gets vaccinated, we believe that only a small proportion of individuals will be excluded. If the proportion of vaccinated individuals with no matched controls exceeds 10%, we will adjust the choice of matching variables to lower this proportion. This will be done by either widening the age groups or not matching by sex. In theory, methods other than exact matching, such as generalized full matching (59) would offer a viable alternative in such cases. It would also allow matching on more confounders, which would be preferable. We unfortunately cannot use such methods, due to the high computational complexity of our approach and the limited available technical infrastructure.

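### The 10% unmatched trigger pools all vaccinated people, so it would stay silent even if matching on three-digit postal code excluded a large share of MS and IBD patients

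*Protocol article*

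**What the plan says.** Section 2.6.1 describes the matching: "These controls will be matched exactly by age in years, gender, place of residence and disease group". It adds: "Controls will be matched without replacement". Vaccinated people without a control are dropped: "If no suitable control can be identified for a vaccinated individual at the time of vaccination, the individual is not included in the analysis". The section expects few such exclusions, citing the amount of data, the long follow-up and the small proportion vaccinated.

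The safeguard is a single threshold, "If the proportion of vaccinated individuals with no matched controls exceeds 10%, we will adjust the choice of matching variables to lower this proportion", and the permitted response is "This will be done by either widening the age groups or not matching by sex". Neither sentence mentions disease group, and place is not among the variables that may be relaxed.

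Table 2 leaves the resolution of place undecided: "The first three digits of the postal code of an individual or the associated federal state will be used as a rough proxy". Section 2.5.1 reports "approximately 50,000 patients with MS, 300,000 patients with CIRD and 80,000 patients with IBD", of whom about 9,000 fall in more than one group. Section 2.3 describes an insurer "with about 8.6 million insured individuals (status of 2024").

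**The concern.** The primary aim (section 2.1) is effectiveness in people with MS, IBD or CIRD, and its comparison with people without these diseases. Matching is exact on disease group, so a vaccinated MS patient needs an MS control of the same age, sex and place. The potential controls for the three disease groups are far fewer than those for everyone else. A proportion pooled over all vaccinated people is dominated by the non-diseased, who will nearly always find a control.

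The check could therefore report an acceptable figure while MS and IBD are heavily thinned. The estimand in Table 1 is the ATT. If exclusion is selective, the ATT in MS and IBD would refer mainly to patients in populous areas and at common ages, while the non-diseased comparator stays almost complete. The disease-specific estimates and their contrast with the non-diseased would also lose precision.

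**Working it through.** The plan gives no expected unmatched share and no uptake figures, so there is no result to reproduce; the 10% is a chosen threshold.

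**Inputs from the documents.** MS 50,000, IBD 80,000, CIRD 300,000, overlap about 9,000 (section 2.5.1); 8.6 million insured (section 2.3); threshold 10% (section 2.6.1). Any disease: 430,000 − 9,000 = 421,000. Non-diseased: 8,600,000 − 421,000 = 8,179,000. The disease counts are cumulative over 2013–2021 and the insured total is a 2024 figure, so shares are approximate.

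**Step 1: what total loss of MS and IBD adds to the pooled proportion.** Let r be the uptake in all diseased people relative to the non-diseased (assumed). The MS+IBD share of the vaccinated is 130,000r / (421,000r + 8,179,000).

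| r | Share of all vaccinated |
|---|---|
| 1 | 130,000 / 8,600,000 = 1.5% |
| 2 | 260,000 / 9,021,000 = 2.9% |
| 3 | 390,000 / 9,442,000 = 4.1% |
| 4 | 520,000 / 9,863,000 = 5.3% |

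With an assumed base of 7.0 million, r = 4 gives 520,000 / (1,684,000 + 6,579,000) = 6.3%. For MS and IBD alone to make up 10% of the vaccinated, their uptake relative to everyone else would have to be (0.1/0.9) × 8,470,000 / 130,000 = 7.2. This step needs no assumption about postal areas.

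**Step 2: expected cell size under postal-code matching.** Mean cell = N / (areas × 70 ages × 2 sexes). With an assumed 670 areas, the divisor is 93,800: MS 0.53, IBD 0.85, CIRD 3.2, non-diseased about 87. Under an even spread, the chance that nobody else is in the cell is exp(−mean): 59%, 43%, 4% and about 0%.

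**Step 3: simulated daily 1:1 exact matching without replacement.** Assumptions: 16 federal states, or 400 to 900 postal areas of uneven size; bell-shaped age distributions; 5% or 30% uptake; 70% or 100% of the listed patients eligible. Ranges run over uptake and eligibility.

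| Place | MS unmatched | IBD unmatched | CIRD unmatched |
|---|---|---|---|
| 400 areas | 28–44% | 23–37% | 4–9% |
| 670 areas | 41–57% | 36–51% | 7–17% |
| 900 areas | 51–64% | 44–60% | 11–22% |
| 16 states | 0.4–1.3% | 0.1–0.5% | at most 0.1% |

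The non-diseased, simulated at the density of 670 areas, lose under 0.1%.

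**Step 4: the pooled proportion in these scenarios.**
- 670 areas, equal uptake of 30%, all eligible: (50,000 × 0.472 + 80,000 × 0.412 + 300,000 × 0.113 + 8,179,000 × 0.0003) / 8,600,000 = 92,914 / 8,600,000 = 1.1%.
- Worst case, 900 areas and r = 4: 4 × (50,000 × 0.643 + 80,000 × 0.600 + 300,000 × 0.220) / 9,863,000 = 584,600 / 9,863,000 = 5.9%. On the 7.0 million base it is 584,600 / 8,263,000 = 7.1%.

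The trigger does not fire in any of them.

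**Step 5: the listed relaxations, if they were used.** At 670 areas with 70% eligible, dropping sex leaves MS 37–41% and IBD 26–33% unmatched. Five-year age bands leave 13–20% and 10–15%; ten-year bands leave 6–10% and 4–7%.

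**The case against.** The strongest reply is that the harm depends on a choice the plan has not made. Table 2 allows federal state, and with it almost nobody is lost. That stands: heavy loss is conditional on postal code, and the number of areas is an assumption.

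A reader might infer that most MS and IBD patients would be lost. The documents do not support this. Losses above one half appear only in the sparser assumed scenarios; with 400 areas they are 23–44%.

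A reader might also infer that the rule can never detect failure in the diseased groups. That is too strong for the three groups together. If all of them went unmatched, the pooled figure would pass 10% once their uptake exceeded (1/9) × 8,179,000 / 421,000 = 2.2 times that of the rest, or 1.7 times on a 7.0 million base. The documents give no uptake ratio. CIRD is not expected to be lost on that scale, however (4–22% in the postal-code scenarios), and the statement does hold for MS and IBD.

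Nor is the listed fallback useless. Ten-year age bands largely repair the matching even at postal-code level, so the absence of place from the list is secondary. But the fallback is used only if the trigger fires.

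Finally, section 2.6.2 describes the matched data by treatment group and disease status and plots numbers over time. This would show how many were matched in each group, but it does not commit to unmatched shares by group and prompts no action. The medication analysis repeats the whole analysis by disease group and medication severity. If that includes new matching, the rule may act within those strata, but not in the primary analysis.

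**Conclusion.** The concern holds in a limited form. The pooled 10% rule is blind to MS and IBD: total loss of both adds about 1.5 points at equal uptake and about 5 points at fourfold uptake. This rests on the plan's own counts and on reading its sentence as written, with no breakdown by disease group.

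The possible size of the loss rests on assumptions. With three-digit postal code it is roughly a quarter to two thirds of vaccinated MS and IBD patients (MS 28–64%, IBD 23–60%, over 400 to 900 areas); with federal state it is about 1% or less. The documents do not show that the loss will occur. They show that, if it did, the stated safeguard would not respond.

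**What to change.** In section 2.6.1, apply the 10% rule separately to MS, IBD, CIRD and the non-diseased within each emulated trial (the zoster trial and each influenza season), and report the unmatched share for each group. In Table 2, settle before matching whether place means three-digit postal code or federal state. Add coarsening of place to federal state to the permitted relaxations, alongside widening age or dropping sex. No order among the three need be prescribed.

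The cost is a few sentences of plan text and, where a group exceeds 10%, a rerun of the matching. The downside of coarsening place is weaker regional control by matching; place should then be kept as a covariate in the Cox model.

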#### 2.6.2 Analysis method

The matching process described above reduces the time-dependent vaccination variable to a time-fixed binary variable, allowing the use of well known analysis methods. We will first describe the matched data using descriptive statistics, stratified by treatment group and disease status. Means and standard deviations will be calculated for normally distributed continuous variables, median and ranges will be used for non-normally distributed continuous variables and counts and percentages will be calculated for categorical and binary variables. Appropriate statistical tests, such as *t*-tests and chi-squared tests, will be used to formally compare the distribution of these variables at baseline. Histograms and boxplots, stratified by both treatment groups and disease groups will also be drawn. In addition, the number of vaccinated individuals, matched controls and number of potential controls evolving over time will be graphically displayed as recommended by Thomas et al. (56).

For the estimation of the vaccine-effectiveness, we will employ standard time-to-event analysis methods, such as Kaplan-Meier curves and Cox models. No complex marginal structural models or similar strategies are required, because only information before inclusion into the trial is used for adjustment, making it impossible for *treatment-confounder* feedback (32) to occur.

Because we only match by age in years, gender, place of residence and disease status, we still have to adjust for the other confounders mentioned earlier to obtain unbiased estimates of the average causal effect we are interested in. A Cox model using the time to the respective outcome of interest as dependent variable and the treatment variable, the disease status and all relevant confounders (as observed at trial inclusion) as independent variables will be used to perform this adjustment. Since we are interested in the effect-modification of the vaccine effectiveness by disease status, we will also include an interaction term of these two variables in the model. This model, in conjunction with an estimate of the baseline hazard function (60), will then also be used to estimate confounder-adjusted survival curves using g-computation (61). These curves will then be used to derive time-dependent relative risk estimates, which will in turn be used to derive the vaccine effectiveness as (62):

(1)
$$\begin{array}{l} \theta \left(t\right)=1-RR\left(t\right), \end{array}$$

by disease status, where *t* denotes the point in time and *RR*(*t*) is the relative risk of experiencing the respective outcome at time *t* in the vaccinated vs. unvaccinated group. Formal contrasts of the disease specific vaccine effectiveness estimates will then also be calculated. Cluster-robust standard errors will be used in the Cox model to adjust for potential dependencies introduced by matching (63). Non-parametric bootstrapping will be used to derive confidence intervals for the vaccine effectiveness and their formal comparisons. Although Abadie and Imbens (64) demonstrated analytically that bootstrapping is not a valid strategy to estimate standard errors in matched samples, it has been shown to work well in simulation studies (65). Due to these simulation results and a lack of alternatives we will therefore still rely on this method.

A very similar analysis strategy will be used to assess the moderating effect of the prior use of immunosuppressive medication on the vaccine effectiveness. In this analysis, only individuals with MS, IBD, or CIRD will be included. The entire analysis described above is then repeated, stratified by disease group and the severity of the received immunosuppresive medication (if any). Additionally, g-computation will be used to estimate the age-specific vaccine-effectiveness in each trial. To obtain a single estimate for the influenza vaccine, we will also use standard meta-analytic approaches to combine the estimates obtained from each of the four emulated influenza trials.

The proportional hazards assumption will be checked using Schoenfeld residual plots (66). If the assumption is deemed violated, we will try different strategies, such as inclusion of time-dependent hazard-ratios and variable transformations, to alleviate this issue. If these methods are unsuccessful, other models such as the additive hazards model (67) with a similar specification will be employed instead. In addition, we will perform a sensitivity analysis in which we will use a weighted Kaplan-Meier estimator instead of g-computation (68), where the weights will be estimated using entropy balancing (69).

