Treatment Assignment	Individual randomization, stratified on disease status (MS, IBD, CIRD or none of these).	To emulate randomization we adjust for multiple confounders using a combination of matching and g-computation.
Start and end of trial	(1) Herpes zoster vaccine effectiveness trial: 01.12.2018–31.12.2021^a^ (2) Influenza vaccine effectiveness trials:*^b^* (a) 01.09.2015–31.05.2016 (b) 01.09.2016–31.05.2017 (c) 01.09.2017–31.05.2018 (d) 01.09.2018–31.05.2019	
Start and end of follow-up	Start of follow-up: time of assignment to treatment strategy. End of follow-up: The earliest of death, loss-to-follow-up or administrative end-of-follow-up (end of the respective study).	
Outcomes	(1) Herpes zoster vaccine effectiveness: medically attended Herpes zoster infection (2) Influenza vaccine effectiveness: (a) medically attended influenza infection (b) severe medically attended influenza infection	
Causal contrast	(1) The ratio between the vaccine effectiveness (1 - the relative risk to develop the outcome at time *t* given the treatment) in the diseased group (individual has either MS, IBD or CIRD) and the non-diseased group (2) The vaccine effectiveness for each of the three disease groups (MS, IBD, CIRD), stratified by the categorized severity of received medication in regards to immunosuppressive effect. Both contrasts will be estimated as *intention-to-treat* and *per-protocol* effects. The target estimand is the average causal effect on the treated (ATT).	
Statistical analysis	Computing formal contrasts of simple Kaplan-Meier estimates.	Time-dependent 1:1 matching by days without replacement. Controls will be matched exactly by age in years, biological sex, place of residence, and disease status. The matched sample will be analyzed using a Cox model with additional adjustment for further confounders. G-computation based on this Cox model and a non-parametric estimate of the baseline hazard will be used to estimate the target estimand. Both *intention-to-treat* and *per-protocol* effects will be estimated by different censoring schemes as described in Section 2.6.3.
Sensitivity analysis	None.	The entire analysis will be repeated using *medically attended urinary tract infection* as a negative control outcome to assess the robustness of the confounder adjustment employed.

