**HSB (Healthcare-seeking behavior)**	
Healthcare seeking behavior, defined as the individuals propensity to seek medical care when ill or perceived ill.	Although not directly observable, several indicators of HSB can be identified from the data (80). We will consider: (1) The number of primary care physician visits in the year before study entry (48). (2) The total number of visits to a physician in the year before study entry. (3) Whether the individual has received a pneumococcal vaccination in the 2 years before study entry, similar to recommendations by World Health Organization (30). (4) Whether the individual has participated in a voluntary preventive medical check-up as coded by the “Einheitliche Bewertungsmaßstab Ziffer” (EBM) number 01732 in the last 2 years.

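### The primary Cox model gives each unmatched confounder one slope for diseased and non-diseased people, so unequal residual confounding can enter the vaccine-effectiveness contrast

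*Protocol article*

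**What the plan says.** Section 2.6.1 of the protocol article sets the matching: "These controls will be matched exactly by age in years, gender, place of residence and disease group", on the day of vaccination. Section 2.6.2 then says that "we still have to adjust for the other confounders mentioned earlier", and gives that job to one Cox model containing "the treatment variable, the disease status and all relevant confounders (as observed at trial inclusion) as independent variables". Because modification by disease is the question, "we will also include an interaction term of these two variables in the model", the two variables being treatment and disease status. No other interaction and no stratified baseline hazard is named. Survival curves and VE by disease status are g-computed from this model.

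Table 1 gives the first causal contrast as "The ratio between the vaccine effectiveness (1 - the relative risk to develop the outcome at time" t, in diseased against non-diseased people.

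Section 2.6.2 also plans a secondary analysis among the diseased only ("The entire analysis described above is then repeated, stratified by disease group" and by severity of immunosuppressive medication), and a sensitivity analysis using a weighted Kaplan-Meier estimator with entropy-balancing weights. Section 2.6.6 plans a negative control outcome, urinary tract infection.

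**The concern.** Age, sex, place and calendar day are balanced by design inside each disease group. The remaining measured confounders in Table 2 are handled in the primary analysis only by the regression, and the regression gives each of them a single coefficient.

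There is reason to doubt that one coefficient fits all groups. Table 2 uses "The total number of visits to a physician in the year before study entry" as a marker of healthcare-seeking behaviour. In people with a chronic inflammatory disease the same count may also reflect monitoring of that disease; this is a clinical inference and is not stated in the article. Section 2.1 itself says that many MS, IBD and CIRD patients take immunosuppressants and that disease and medication effects need to be separated. Table 2 describes the vaccination-plan confounder only for patients with these diseases.

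A wrong slope in one group leaves confounding in that group's vaccine effect. The vaccine by disease term is the one term free to absorb the difference, and it is also the primary question. The error is systematic, so the large sample does not shrink it.

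**Working it through.** The article states no figure on this point, so there is nothing to reproduce. The check asks what the specified model returns when true VE is the same in both groups.

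**Inputs from the article.** Model form and matching variables as above. Section 2.5.1 reports "approximately 50,000 patients with MS, 300,000 patients with CIRD and 80,000 patients with IBD", about 9,000 of them in more than one category; Section 2.3 reports about 8.6 million insured. (50,000 + 300,000 + 80,000 − 9,000) / 8,600,000 = 4.9%. This is a source-population share, with cases counted over 2013–2021 and the insured as of 2024. The share in the matched sample is not given, so 5% is an assumption, varied below.

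**Other assumed inputs.** One unmatched confounder X with SD 1 and mean δ higher in vaccinated people than in controls; log hazard ratio per SD of b_N in the non-diseased and b_D in the diseased; similar event rates in both groups; an outcome uncommon enough that hazard ratio and risk ratio nearly coincide.

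**Formula.** With a common slope b*, the fitted VE in group g is approximately

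VE_g = 1 − (1 − VE) × exp[(b_g − b*) × δ], with b* ≈ 0.95 b_N + 0.05 b_D.

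Worked case: b_N = 0.4, b_D = 0.1, δ = 0.4, true VE = 0.40.
- b* = 0.95 × 0.4 + 0.05 × 0.1 = 0.385
- Non-diseased: 1 − 0.6 × exp(0.015 × 0.4) = 1 − 0.6 × 1.0060 = 0.396
- Diseased: 1 − 0.6 × exp(−0.285 × 0.4) = 1 − 0.6 × 0.8923 = 0.465
- Ratio: 0.465 / 0.396 = 1.17 (truth 1)

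| b_N | b_D | δ | VE non-diseased (true 0.40) | VE diseased (true 0.40) | Ratio at VE 0.40 | Ratio at VE 0.70 |
|---|---|---|---|---|---|---|
| 0.20 | 0.15 | 0.15 | 0.400 | 0.404 | 1.01 | 1.00 |
| 0.20 | 0.15 | 0.30 | 0.400 | 0.408 | 1.02 | 1.01 |
| 0.20 | 0.10 | 0.30 | 0.399 | 0.417 | 1.04 | 1.01 |
| 0.30 | 0.10 | 0.40 | 0.398 | 0.444 | 1.12 | 1.03 |
| 0.40 | 0.10 | 0.40 | 0.396 | 0.465 | 1.17 | 1.05 |
| 0.10 | 0.30 | 0.30 | 0.402 | 0.365 | 0.91 | 0.97 |
| 0.10 | 0.30 | 0.40 | 0.402 | 0.353 | 0.88 | 0.96 |

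Solving the model's likelihood equations numerically in the rare-event limit gives the same ratios to two decimals.

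**Matched variables.** With δ = 0 the exponential is 1 whatever the slopes, so the ratio is 1.

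**Diseased share.** With the same δ in both groups, the two apparent hazard ratios differ by the factor exp[(b_D − b_N) × δ], in which b* cancels. In the worked case at a 30% share, b* = 0.7 × 0.4 + 0.3 × 0.1 = 0.31. The VEs are 1 − 0.6 × exp(0.036) = 0.378 and 1 − 0.6 × exp(−0.084) = 0.448, a ratio of 1.19.

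**Disease-specific slopes.** Setting b* = b_g makes the exponent zero. Both groups return 0.400 and the ratio is 1.00 in every row.

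**Cross-check with a larger slope gap.** For a binary confounder present in 50% of vaccinated people and 30% of controls, with hazard ratio 2 in the non-diseased and 1 in the diseased, the pooled value is 0.95 × 2 + 0.05 × 1 = 1.95.
- Confounding factors (1 + 0.5(h − 1)) / (1 + 0.3(h − 1)): 1.1538 at h = 2, 1.1479 at h = 1.95, 1 at h = 1
- Non-diseased: 1 − 0.6 × 1.1538 / 1.1479 = 0.397
- Diseased: 1 − 0.6 / 1.1479 = 0.477
- Ratio: 1.20

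Simulated Cox models with g-computation on the treated for this case (25 runs, n = 60,000) gave 1.23 (Monte Carlo SE 0.03), against 1.03 (SE 0.035) once a confounder by disease term was added.

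**The case against.** **The size is assumed.** This stands. The article gives no confounder effect, imbalance or event count. The sign flips with the order of the slopes, similar slopes give ratios of 1.01 to 1.02, and at VE 0.70 the effect is small throughout.

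**The article is a summary.** It does not exclude further interactions, and a full plan might add them. This stands in part. But the model is stated, one interaction is singled out, and the primary contrast is said to come from that model. The additive hazards fallback keeps a similar specification.

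**Checks are already planned.** The entropy-balanced Kaplan-Meier analysis uses no Cox slopes, and repeating the analysis on urinary tract infection could show residual confounding that differs by group. Both may raise an alarm. Neither corrects the primary estimate, balancing within disease group is not stated, and confounder slopes for the negative control may differ from those for the real outcome. Schoenfeld plots check proportional hazards, which is a different matter.

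A reader might also infer three stronger things, which the article does not support:
- *Every confounder is affected.* Age, sex and place are matched exactly within disease group and create no such bias.
- *The slopes come almost wholly from the non-diseased.* The composition of the matched sample is not given. The claim also fails for immunosuppressants: if about 1% of the non-diseased and 35% to 50% of the diseased used them (assumed), then at a 5% share the diseased would be 0.0175 / (0.0175 + 0.0095) = 65% to 0.025 / (0.025 + 0.0095) = 72% of users. Nor is the claim needed, since the ratio barely depends on the share.
- *Primary and secondary VE for the same disease will conflict.* The secondary analysis is also split by medication severity, so it estimates something else. It contains no non-diseased people and cannot serve as a check on the contrast.

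**Conclusion.** The point holds for unmatched confounders. As written, the primary model lets only the vaccine effect vary by disease. An unmatched confounder that is both unbalanced by vaccination and different in effect by disease would therefore shift the VE ratio when no true difference exists. Under the tabulated assumptions the shift runs from about 0.88 to 1.17 at VE 0.40 and from 0.96 to 1.05 at VE 0.70; a more extreme binary confounder gives 1.20 at VE 0.40. These figures show what is possible and do not predict the bias. They rest on assumed slopes and imbalances, one confounder at a time, and an uncommon outcome. Neither direction nor size can be fixed from the article. The change is worth making because the affected term is the primary question and the remedy uses data already in hand.

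**What to change.** - In the primary analysis, fit the Cox model separately by disease group, or stratify the baseline hazard by disease and add disease by confounder interactions for the unmatched confounders. Then g-compute and contrast. Pairs are already matched within disease group, so no re-matching is needed.
- Use the same estimator for every group in a contrast. If a group has too few events, use a reduced or penalised set of interactions, or use within-disease entropy balancing for all groups in that contrast. Changing method for the sparse group alone would create a between-group difference of its own.
- State that the entropy balancing is done within disease group.
- State how the roughly 9,000 patients in more than one disease category enter the group-specific fits.
- Keep the common-slope model as a sensitivity analysis.

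The cost is specification wording, some computing and some loss of precision in the smaller disease groups. That loss has not been quantified here, because the article gives no event counts. No new data are needed.
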